#### Safety laboratory and urine analysis:

Clinical laboratory test results will be marked whether the result is below, within or above the respective reference range. The number of values outside of the reference range will be counted.

RESTRICTED BUSINESS PROPRIETY

## ECG

The ECG will be evaluated by a centralized procedure. The transmitted standard ECG results like PQ, QRS, QT and QTc duration and heart rate will be summarized per visit and treatment group.

The number of subjects with normal/abnormal ECGs and clinically significant ECGs (resulting in AEs) will be compared between treatment groups by means of the exact test of Fisher (or its normal approximation, the chi-squared test).

Detailed descriptive analysis of the reasons (category) of abnormality will be done.

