### 3. Study design

#### 3.1 Experimental design

This study is an open-label, controlled, phase II clinical trial to evaluate immunogenicity and safety of MVA-BN® (IMVAMUNE®) smallpox vaccine in 18-40 year old subjects with diagnosed atopic dermatitis.

The following two subject groups are compared:

Group 1: Healthy, vaccinia naïve subjects without atopic disease

Group 2: Vaccinia naïve subjects with diagnosed atopic dermatitis. “Diagnosed” atopic dermatitis includes subjects with either history of or subjects with currently active (defined as SCORAD  $\leq$  30, Kunz et al., 1997) atopic dermatitis.

[figure not shown]

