### All study subjects:

3. Male and female subjects between 18 and 40 years of age without history of smallpox vaccination.
4. Women must have a negative serum pregnancy test at screening and a negative urine pregnancy test within 24 hours prior to vaccination.
5. Women of childbearing potential must have used an acceptable method of contraception for 30 days prior to the first vaccination, must agree to use an acceptable method of contraception during the study, and must not become pregnant for at least 28 days after the last vaccination. A woman is considered of childbearing potential unless post-menopausal or surgically sterilized. (Acceptable contraception methods are restricted to abstinence, barrier contraceptives, intrauterine contraceptive devices or licensed hormonal products.)
6. Read, signed and dated informed consent document after being advised of the risks and benefits of the study in a language understood by the subject signed, and prior to performance of any study specific procedure.
7. Troponin I  $< 2$  fold ULN.
8. White blood cells  $\geq 2500/\text{mm}^3$  and  $< 11,000/\text{mm}^3$ .
9. Absolute neutrophil count (ANC) within normal limits.
10. Negative urine glucose by dipstick or urinalysis.
11. Hemoglobin within normal limits.
12. Platelets within normal limits.
13. Adequate renal function defined as:
  - a. Serum creatinine without clinically significant findings
  - b. Urine protein  $< 30$  mg/dL or none or trace proteinuria (by urinalysis or dip stick)
14. Adequate hepatic function defined as:
  - a. Total bilirubin  $\leq 1.5 \times$  ULN in the absence of other evidence of significant liver disease
  - b. AST (SGOT), ALT (SGPT) and alkaline phosphatase without clinically significant findings
15. Electrocardiogram (ECG) without clinically significant findings (e.g. any kind of atrioventricular or intraventricular conditions or blocks such as complete left or right bundle branch block, AV-node block, QTc or PR prolongation, premature atrial contractions or other atrial arrhythmia, sustained ventricular arrhythmia, 2 premature ventricular contractions (PVC) in a row, ST elevation consistent with ischemia).
16. Availability for follow-up for the planned duration of the study (26 weeks after last vaccination).

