### 6.4 Dose, vaccination schedule and route of administration

Subjects of both study groups will receive two s.c. vaccinations with 0.5 ml MVA-BN® (IMVAMUNE®) vaccine containing  $1 \times 10^8$  TCID50, four weeks apart (Visit 1 / Day 0 and Visit 3 / Visit 1 + 28-35 days) in the non-dominant upper arm (deltoid region). Details on vaccine administration can be found in Bavarian Nordic's SOP, SOP/CLIN/16, entitled "Storage, Handling and Preparation of Liquid Frozen MVA-BN for Vaccination".

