### **7.1.4 ECG assessments**

A standard 12-lead ECG will be taken on all subjects at screening (Visit SCR) and 7 - 14 days after each vaccination (for Visit 2: 7-10 days and Visit 4: V3+10-14 days). For Visit 5 and the follow-up visit, an ECG is only done if clinically indicated.

ECGs will be evaluated by a centralized procedure. Unclear ECG abnormalities will additionally be evaluated by a central Cardiologist. The workflow / communication flow will be provided in a separate manual.

If clinically indicated, or in case of any kind of cardiac symptoms such as but not limited to chest pain, dyspnoea, arrhythmia, or edema subjects will be referred for a cardiac evaluation by a Cardiologist and further diagnostic tests will be done as recommended by this Cardiologist (e.g. (treadmill) ECG, cardiac enzymes, echocardiogram). Subjects will then be followed up for at least one year in a frequency determined by the Cardiologist.

Such adverse events fulfill the definition of an “adverse event of special interest” and are to be handled respectively reported as described under section 8.4.

Using replication-competent vaccinia-based smallpox vaccines during smallpox vaccination programs in the US during the last years, cases of acute myocarditis and pericarditis were observed (Grabenstein and Winkenwerder, 2003).

Case definitions as published by the US Center of Disease Control (CDC) ("Update: Cardiac-Related Events During the Civilian Smallpox Vaccination Program --- United States, MMWR May 30, 2003, Vol. 52, No. 21, p. 494") are provided in Appendix II in order to:

- help Investigators to recognize possible events of acute myocarditis and/or pericarditis and
- distinguish from unspecific and isolated ECG changes without or with unclear clinical meaning

Subjects who develop any kind of cardiac symptoms during the study such as but not limited to chest pain, dyspnea, arrhythmia, or edema are referred to a Cardiologist for cardiac evaluation including (treadmill) ECG, cardiac enzymes and echocardiogram. Depending on the results of this evaluation further diagnostic tests will be done as recommended by the Cardiologist and patients will be followed up for at least one year in a frequency determined by the Cardiologist. Furthermore unclear ECG abnormalities observed during the study will be examined upon recommendation of the cardiologist.

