## 8. Adverse event definitions and reporting

Any change in health observed before first vaccination will be recorded in the “baseline signs and symptoms” section of the CRF and will not be considered an adverse event.

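### The between-group test on normal/abnormal ECGs is not tied to the screening ECG, so benign abnormalities present before vaccination can mimic or mask a difference between atopic dermatitis and healthy subjects

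*Protocol*

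**What the plan says.** The ECG paragraph of protocol section 9.4.3 makes three statements.

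- Intervals and rate: PQ, QRS, QT, QTc and "heart rate will be summarized per visit and treatment group".
- The test: "The number of subjects with normal/abnormal ECGs and clinically significant ECGs (resulting in AEs) will be compared between treatment groups", by Fisher's exact test or its chi-squared approximation.
- Description: "Detailed descriptive analysis of the reasons (category) of abnormality will be done".

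The per-visit wording belongs to the first statement only. The tested count has no visit, no baseline condition and no requirement that the abnormality be new.

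Other sections supply the context.

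- Section 7.1.4: "A standard 12-lead ECG will be taken on all subjects at screening (Visit SCR) and 7 - 14 days after each vaccination". The post-vaccination recordings are at Visits 2 and 4, and reading is centralised. The Visit SCR list in section 3.2.1 calls the screening recording the baseline ECG.
- Section 4.2, inclusion 15, requires an "Electrocardiogram (ECG) without clinically significant findings", with a list of examples.
- Section 3.1: "The following two subject groups are compared", namely healthy subjects and subjects with AD.
- Section 6.4: "Subjects of both study groups will receive two s.c. vaccinations".

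**The concern.** Section 9.4.3 separates abnormal ECGs from clinically significant ones, so the plan recognises a class that is abnormal but not significant. Inclusion 15 lets that class in. Take a subject with the same benign finding at screening, Visit 2 and Visit 4. In the tested count this subject looks the same as one who was normal at screening and became abnormal after vaccination.

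In a randomised trial, such static findings would on average be balanced and would only add noise. Here membership of a group is a matter of disease, so equal rates before vaccination cannot be assumed. Two errors become possible. A baseline difference between AD and healthy subjects can be read as a difference in response, or a common static finding can dilute a real difference in new abnormalities.

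The protocol uses prior status elsewhere. Section 7.1.1 places the baseline assessment of safety parameters at screening, and the ECG criteria for possible myocarditis in Appendix II require abnormalities that were not documented before. The normal/abnormal comparison makes no such link.

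**Working it through.** The protocol gives no ECG abnormality rate, effect size or power, so there is no figure of its own to reproduce. The calculation below is an illustration.

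**Inputs from the protocol.** The group sizes come from the lot-exchange table in Appendix V: healthy 105 + 125 = 230, AD 72 + 258 = 330, total 560. The test is Fisher's exact test (section 9.4.3).

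**Assumed inputs.** b is the proportion with a benign abnormality at screening, taken to persist. e is the rate of new abnormality among subjects normal at screening. The level is two-sided 5%. Every b and e is an assumption.

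**Formulas.** Counted without regard to screening, a subject is abnormal with probability q = b + (1 − b)e. Counting only new abnormalities, the rate is e among n(1 − b) subjects. Power is the exact sum, over both binomial distributions, of the probability of outcomes with Fisher p ≤ 0.05.

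**Step 1: masking, equal b in both groups, e = 2% (healthy) versus 8% (AD).** At b = 10%, q is 0.10 + 0.90 × 0.02 = 11.8% versus 0.10 + 0.90 × 0.08 = 17.2%. The new-abnormality count uses 230 × 0.90 = 207 and 330 × 0.90 = 297 subjects.

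| b | q healthy vs AD | Power, count as written | Power, new abnormalities |
|---|---|---|---|
| 0% | 2.0% vs 8.0% | 89.7% | 89.7% |
| 10% | 11.8% vs 17.2% | 40.4% | 85.8% |
| 20% | 21.6% vs 26.4% | 24.0% | 80.8% |
| 30% | 31.4% vs 35.6% | 16.6% | 74.8% |
| 40% | 41.2% vs 44.8% | 12.8% | 66.9% |

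With e = 2% versus 6%, the corresponding powers at b = 0, 10, 20, 30 and 40% are 62.5, 20.9, 13.0, 9.7 and 8.1% as written, against 62.5, 57.4, 51.8, 45.1 and 37.2%.

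**Step 2: mimicry, e = 2% in both groups, unequal b.** At 20% versus 30%, q is 0.20 + 0.80 × 0.02 = 21.6% versus 0.30 + 0.70 × 0.02 = 31.4%.

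| b healthy vs AD | P(p ≤ 0.05), count as written | P(p ≤ 0.05), new abnormalities |
|---|---|---|
| 20% vs 20% | 4.4% | 3.1% |
| 20% vs 25% | 24.8% | 3.5% |
| 20% vs 30% | 71.7% | 3.6% |
| 10% vs 15% | 34.5% | 3.6% |
| 10% vs 20% | 85.5% | 3.7% |

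The last column of each table counts new abnormalities in subjects normal at screening. It does not model worsening in subjects already abnormal.

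**The case against.** The strongest reply is that the paragraph is silent rather than wrong. It does not say that the screening ECG is disregarded, and a count by visit with screening as its own row would fit the text. Section 9.4.4 refers to a statistical analysis plan, which is not at hand and may settle visits and baseline handling. This part stands: a reader might infer that the plan excludes the screening ECG, and the text does not support that. But the protocol does fix a test, a unit, a contrast and an outcome, and that outcome is prevalence. A by-visit version would expose a baseline imbalance, yet each test would still compare prevalence rather than change.

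A reader might also infer that the trial's cardiac safety assessment is compromised. It is not. Clinically significant ECGs are barred at entry, and section 8 says that a change in health seen before the first vaccination is a baseline sign "and will not be considered an adverse event". Cardiac symptoms, clinically significant ECG changes and raised cardiac enzymes are events of special interest (section 8.4) and have their own Fisher comparison in section 9.4.3. Only the benign normal/abnormal count is exposed.

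A third tempting inference is that pre-existing abnormalities swamp a vaccine effect. Both groups are vaccinated, so the test contrasts AD with healthy subjects and would not isolate a vaccine effect even with screening taken into account.

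Finally, the rates are assumed. Subjects are 18 to 40 years old, the examples in inclusion 15 remove many abnormalities, and exclusions 10 to 12 remove cardiac history and risk. The remaining baseline rate could be low. This stands too, and it limits what can be said about size.

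**Conclusion.** The point holds in a narrow form. The normal/abnormal ECG comparison is specified without reference to screening and without naming visits, in non-randomised groups whose entry rule admits benign abnormalities. It can therefore mimic or mask a difference between AD and healthy subjects in ECG change after vaccination.

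If 10% to 30% of subjects carry a persistent benign abnormality and new onset is 2% versus 8%, power falls to between 17% and 40%, where a new-abnormality count would have 75% to 86%. A baseline imbalance of 5 to 10 points, with equal new onset, gives a nominally significant result in about 25% to 86% of trials. With no baseline abnormality there is no loss. These figures show direction and plausible range; the documents do not allow an estimate for this trial.

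Severity is low to moderate. ECG normal/abnormal status is not among the safety endpoints listed in section 9.2.2, and no decision rule rests on the p-value.

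**What to change.** In the ECG paragraph of section 9.4.3:

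1. Define the compared outcome as an ECG abnormality at Visit 2 or Visit 4 that is new or worsened relative to the screening ECG.
2. Add a shift table from screening by group, including subjects abnormal at screening.
3. Also summarise PQ, QRS, QT, QTc and heart rate as change from screening.
4. Keep the total abnormal count by visit, with screening shown, as descriptive.

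No new data are needed, because ECGs at screening, Visit 2 and Visit 4 are already scheduled for all subjects with centralised evaluation. The cost is some wording, slightly more analysis work, and a rule set in advance for judging worsening in subjects already abnormal at screening.

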### **9.4.4 Data handling**

All data obtained in this study and documented in the case report forms (CRFs) will be listed. For parameters of interest, summary tables with descriptive group statistics (mean, standard deviation, minimum, maximum, number of valid cases) for metrical variables will be prepared. For ordinal/dichotomous variables summary tables showing the absolute and relative count in each category will be prepared.

Further statistical analysis may be performed as appropriate.

**Kendle Inc. and GmbH** will be responsible for data management and statistical evaluation. Data will be analysed using SAS® PC. The procedure for accounting for missing, unused and spurious data will be given in the Statistical Analysis Plan.

## **10. Ethical aspects**

### **10.1 Ethical and legal regulations**

The Principal Investigators make sure that this clinical trial is conducted in complete accordance with the provisions of the Declaration of Helsinki (and its amendments of Tokyo, Venice, Hong Kong, Somerset West and Edinburgh), the national laws and other guidelines for the conduct of clinical studies like the ICH Harmonised Tripartite Guideline for Good Clinical Practice to guarantee the greatest possible subject protection.

### **10.2 Approval of an Independent Ethics Committee (IEC) / Institutional Review Board (IRB)**

The protocol must be reviewed by the competent IEC / IRB according to the national law of the respective site before the first subject is included in this study.

If one of the Investigators is a member of one of these committees, he may not vote on any aspect of the review of this protocol.

The Sponsor will assure that the IEC / IRB is informed of any amendment to the protocol and any unanticipated problems involving risks to human subjects included in the study. Such information will be provided to the committee at intervals appropriate to the degree of subject risk involved, but not less than once a year. Copies of all correspondence between the Investigator and the committee must be forwarded immediately to the sponsor. In case of withdrawal of IEC / IRB approval of the study, the sponsor has to be contacted immediately by facsimile or telephone.

### **10.3 Confidentiality and data protection**

The Principal Investigator of the respective site is obliged to ensure anonymity of the subject. He/she has to make sure that all documents including CRFs provided (e.g. in the course of a marketing authorization procedure) to third parties (in this case: to the manufacturer of MVA-BN® (IMVAMUNE®) or to an authority) contain no subject names.

Only a subject and center number, not by their name or clinic and subject's file number, may identify subjects respectively. The Principal Investigators keep separate confidential subject logs for study enrollment, which allows subject numbers to be matched with names and addresses of subjects at any time. Documents not meant to be passed on to third parties have to be stored confidentially by the Principal Investigator.

Any information collected in the course of the study may be made available only to persons directly involved in this study (Principal Investigator and his staff members, monitor, statistician) or to authorized persons by the sponsor or the Principal Investigator or authorities.

## **11. Informed consent**

No subject can participate in this study without having given informed consent in writing after the Investigator or his delegate has informed the subject clearly and completely, verbally and in writing, over the purpose, procedures, potential benefits and risks of the current study and prior to study drug administration.

One signed original of the informed consent must be given to each subject and one signed original must remain in the study documentation file and be available for verification by the monitor or competent regulatory authorities at any time.

Subjects must be informed unequivocally that they may refuse participation in the study and that they may withdraw from the study at any time and for whatever reason and that withdrawal of consent will not affect their subsequent medical treatment or relationship with the treating physician.

Subjects also consent to authorize the monitor, quality assurance personnel and regulatory authorities to inspect source documents for quality assurance purposes. Such verifications will always be conducted on site and under the ethical supervision of the Investigator. All aspects of the confidentiality of the subject's data will be guaranteed.

The informed consent form will be prepared in accordance with ICH-GCP guidelines and must be approved by the appropriate IEC / IRB.

## **12. Case report forms and retention of records**

### **12.1 Case report forms**

All CRFs are to be filled out completely by the examining personnel, then reviewed and signed by the Principal Investigator to indicate their correctness.

It is the Principal Investigators responsibility to ensure that all subject discontinuations or changes in study or other medications entered on the subject's CRF are also made on the subjects medical records.

The CRFs for any subject leaving the study should be completed at the time of the final visit or shortly thereafter.

### **12.2 Retention of records**

The Investigator shall maintain the records of disposition of drug receipts, drug accountability forms, his copies of the CRFs, subject files and regulatory documents (e.g. informed consents, IEC / IRB approval, FDA1572, Financial Disclosure Forms) according to applicable national law after the end of the study.

### 13. Monitoring of the study

The monitor is responsible for obtaining an overview of the course of the trial in co-operation with the Investigator, checking if the trial protocol is being observed, and helping the Investigators to solve any problems which may arise. All documents in the context with this clinical trial will be handled confidentially at any time.

The Investigator has agreed to give the monitor access to relevant hospital or clinical records to confirm their consistency with the CRF entries and to obtain an adequate overview of the course of the trial. The monitor checks entries on the CRF for completeness, accuracy and correctness. The entries on the CRF will be verified against source documents with respect to the following criteria and in the following frequencies:

|                                 |      |
|---------------------------------|------|
| Informed consent                | 100% |
| Demographic data                | 100% |
| In-/exclusion criteria          | 100% |
| Primary target parameters       | 100% |
| Administration of study vaccine | 100% |
| Adverse events                  | 100% |
| Time points of visits           | 100% |
| Laboratory parameters           | 100% |
| Vital signs                     | 100% |

This will be done under preservation of data protection.

The source data verification must be performed by direct insight. If a subject refuses to consent to this procedure he/she must not be enrolled in the study.

The Investigator (or a representative) has further agreed to support the monitor in solving any problems he/she discovers during his/her visits.

### 14. Responsibilities of the Investigator

The Investigator agrees to carry out the study in accordance with the guidelines and procedures outlined in this trial protocol. The Investigator especially consents to strictly adhere to the ethical principles (see section 10 of this protocol).

The Investigator knows that he/she must, according to professional regulations for physicians, obtain the approval of the competent IEC / IRB.

Any deviation from the trial protocol must, before its implementation, be agreed to by the sponsor in writing, and by the IEC / IRB initially consulted.

Changes to the protocol require written "Amendments to the protocol" and written approval by Principal Investigator. Changes are allowed only if study value is not reduced and if they are ethically justifiable. The statistician must agree to the amendment, if appropriate, his statement is to be submitted to the IEC / IRB. The amendment must be passed on to all participating Investigators with the obligation to adhere to its provisions. If warranted, the subject information has to be changed accordingly.

It is within the responsibility of the Investigator that a CRF is completed and signed after the subject has finished the trial for each subject participating in the study.

All entries on the CRFs must be made in black ball-point pen; corrections are made by placing a single horizontal line through the incorrect entry, so that it can still be seen, and placing the revised entry beside it. The revised entry must be filled in, initialled and dated by a member of the Investigator's research team authorized to make CRF entries. Correction fluid must not be used.

At the conclusion of the study, the Investigator will return all partly used, unused and empty drug containers to the sponsor.

The Investigator may ask to terminate the study due to administrative or other reasons. If this should be the case, appropriate measures which safeguard the interests of the participating subjects must be taken after verification and consultation with the Principal Investigator.

By signing this protocol, the Investigator confirms that he/she has read the entire trial protocol, agrees to its procedures, and will comply strictly with the formulated guidelines.

